#### Secondary Outcome Measures

Secondary outcome measures will be (1) biological outcomes: composition of interdental microbiota (16S ribosomal RNA sequencing, T0 and T3); (2) clinical outcomes: evolution of plaque index, GI, BoP, PPD, and CAL at T1, T2, and T3; and (3) patient-reported outcomes: acceptability and integration of daily interdental cleaning, assessed by the TFA questionnaire at T1, T2, and T3.

### Sample Size

The reduction in gingival bleeding was considered the primary outcome variable, and an estimate of the mean difference in reduction was used to calculate the sample size. Based on a 2-sided α of .05, 80% power, an intraclass correlation of 0.8, and an expected 25% difference in BoP between groups, a total of 50 participants (200 sites) are required. Taking into account a dropout rate of 10%, in order to have 50 participants at the end, 56 participants (28 per group) will be included.

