#### Clinical Assessments (At All Visits)

The oral examination in accordance with clinical practices will be carried out by a dentist who will report the following clinical parameters:

BoP: dichotomous gingival index (GI) reporting the presence or absence of BoP after 30 seconds (0=absence of bleeding after 30 s and 1=presence of bleeding after 30 s). A total of 4 sites are recorded per tooth (mesiobuccal, distobuccal, mesiopalatine, and distopalatine) [14,15].Gingivitis score (GI): measured by visual observation from 0 to 3 (0=no inflammation; 1=slight change, slight inflammation in color, and little change in texture; 2=moderate, moderate inflammation, redness, edema, and hypertrophy, tendency to bleed on probing; 3=severe, marked redness, inflammation, hypertrophy, and tendency to spontaneous bleeding). Gingivitis score=sum of GI scores divided by the number of total sites [16].Dental plaque score (Rustogi Modified Navy Plaque Index): according to the Navy Plaque Index modified by Rustogi et al [17], the presence of plaque deposits is sought on the vestibular and lingual surfaces of the teeth. Each tooth face is divided into 9 areas to which a dichotomous score is assigned (0=absence of plaque and 1=presence of plaque). Thus, for each tooth, 18 measurements are carried out. This index makes it possible to detect minimal differences at the partial level of the marginal or interproximal zones, or at the total level of the oral cavity [17].PPD score: a measure indicating the distance separating the top of the marginal gingiva from the bottom of the periodontal pocket. The measurement is expressed in millimeters. Overall, 4 sites are recorded per tooth (mesiobuccal, distobuccal, mesiopalatine, and distopalatine) [18].CAL score: addition of PPD and recession height, which is the distance separating the enamel-cementum junction from the bottom of the pocket. In total, 4 sites are recorded per tooth (mesiobuccal, distobuccal, mesiopalatine, and distopalatine) [15].Interdental bleeding: bleeding was assessed dichotomously following interdental brushing (0=absence of bleeding after insertion and removal of the brush and 1=presence of bleeding after insertion and removal). All interdental sites were recorded at each visit.

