PPD and CAL will be assessed following the criteria defined by the consensus report of the 2017 World Workshop on the Classification of Periodontal and Peri-Implant Diseases and Conditions [13], using the US Williams PDT sensor probe (Zila-Pro-Dentec Inc) at a pressure of 20 g. Based on severity-defined stages of interdental CAL and tooth loss, complexity, extent, and distribution, they included a full oral examination of 6 sites on each permanent tooth. All measures will be performed on all teeth except for third molars. One calibrated dentist trained will perform the periodontal evaluations of all participants. Intraclass correlation coefficients for PPD and CAL will be determined at the level of the site. The intraexaminer coefficients for CAL will be, respectively, from 0.80 and 0.85, and from 0.75 and 0.85 for probing depth.

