#### Interdental Microbiota Sampling (T0 and T3)

Interdental plaque will be collected from 4 sites (15-16, 25-26, 35-36, and 45-46). Each IDB used for sampling will be stored in RNase- and DNase-free tubes at –20°C within 4 hours and transferred later to the GenEPI platform (Hospices Civils of Lyon, Lyon, France) for long-term storage at −80°C. Analysis will be performed by 16S ribosomal RNA gene sequencing to determine microbiota composition in a single batch. Briefly, a 16S ribosomal RNA gene fragment comprising V3 and V4 hypervariable regions will be amplified using an optimized and standardized 16S amplicon library preparation. Sequencing will then be performed using a 250-base pair paired-end sequencing protocol on an Illumina MiSeq platform (Illumina). Bioinformatic analysis will then be performed using the QIIME2 software (Caporaso Lab, Northern Arizona University) in its latest version.

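### The sample size of 50 participants (200 sites) does not follow from its stated inputs, and its 4 sites per mouth are not the sites of the primary outcome

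*Protocol article*

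**What the plan says.** The Sample Size section of the protocol names the reduction in gingival bleeding as the sizing variable and says that a mean difference in reduction was used. It then sets out the derivation: "Based on a 2-sided α of .05, 80% power", followed by "an intraclass correlation of 0.8, and an expected 25% difference in BoP between groups, a total of 50 participants (200 sites) are required". A 10% dropout allowance raises the number to 56.

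The Primary Outcome Measures section defines the outcome as the proportion of BoP sites at month 3. The Clinical Assessments section says how BoP is recorded: "A total of 4 sites are recorded per tooth (mesiobuccal, distobuccal, mesiopalatine, and distopalatine". It adds: "All measures will be performed on all teeth except for third molars". The only set of four sites per mouth in the document is in the microbiota section: "Interdental plaque will be collected from 4 sites (15-16, 25-26, 35-36, and 45-46".

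**The concern.** The paragraph presents 50 as the result of a calculation, but a reader cannot get from its inputs to its output. A mean difference needs an SD, and a difference of proportions needs a control rate. Neither is given. The two remaining inputs, "an intraclass correlation of 0.8" and "an expected 25% difference in BoP between groups", each have more than one meaning, and the meanings lead to very different sample sizes. The site count, which would normally show which meaning was used, does not match the way the primary outcome is measured.

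This is the article's only justification for the size of the trial. If the result is null, readers will rely on the 80% to judge whether calibration has no benefit or the trial was too small to show one.

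**Working it through.** **Inputs from the protocol.** Two-sided α 0.05; power 80%; correlation 0.8; 25% difference; 50 participants and 200 sites (Sample Size); 1:1 allocation (Randomization). **Assumed here, because not stated:** the control rate or SD, varied over a range.

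**1. Sites per mouth.** 200/50 = 4. The primary outcome has 4 sites per tooth. With at least 20 natural teeth (Exclusion Criteria) and at most 28 without third molars, that is about 4×20 = 80 to 4×28 = 112 per mouth.

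**2. Reading A: 0.8 is clustering of sites within a mouth, 25% is absolute.** Design effect = 1 + (4−1)×0.8 = 3.4. Effective sites = 200/3.4 = 58.8, or n = 29.4 per arm. Power, with the pooled-variance formula:

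Φ{[Δ − 1.96√(2p̄(1−p̄)/n)] / √[(p₁(1−p₁)+p₂(1−p₂))/n]}

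For 30% vs 5%: p̄ = 0.175, null SE = √(0.28875/29.41) = 0.0991, alternative SE = √(0.2575/29.41) = 0.0936. Then (0.25 − 0.1942)/0.0936 = 0.596, so power is 72.5%.

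| Control / calibrated BoP | Power | Participants needed for 80% |
|---|---|---|
| 25% / 0% | 84.5% | 46 |
| 26% / 1% | 81.8% | 50 |
| 27% / 2% | 79.3% | 52 |
| 30% / 5% | 72.5% | 62 |
| 40% / 15% | 57.7% | 84 |
| 50% / 25% | 50.8% | 100 |
| 62.5% / 37.5% | 48.2% (minimum) | 106 |

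The plan's figure of 50 is reproduced at 26% vs 1%. At low rates, 80% needs the calibrated arm to end at about 2% or less. The table mirrors at very high rates (100% vs 75% again gives 84.5%).

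**3. Reading A with the sites actually recorded.** With 112 sites the design effect is 1 + 111×0.8 = 89.8, and 25×112/89.8 = 31.2 effective sites per arm. Power is 75% at 30/5 and 51% at 62.5/37.5. At this correlation the mismatch of sites barely changes power. It matters because the calculation describes a different outcome set.

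**4. Reading B: as A, but 25% is relative.** With 29.4 per arm and both tails counted, power is about 6% at 10% vs 7.5%, rising to 16% at 50% vs 37.5%.

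**5. Reading C: 200 independent sites.** 100 per arm gives 95% or more for any absolute 25-point difference, so the stated 80% does not arise this way.

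**6. Reading D: difference in participant-level means.** Detectable difference with 25 per arm, normal approximation: (1.960 + 0.842)×√(2/25) = 0.79 SD; with the t distribution, 0.81 SD. For 25 points, SD must be at most 25/0.81, about 31 points.

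**7. Reading E: change score, 0.8 as the baseline-to-follow-up correlation.** SD of change = SD×√(2×(1−0.8)) = 0.632×SD. With SD 50 points this is 31.6, which needs 26 per arm (52 in total), and 50 participants give about 80%. With SD 40 points it is 25.3, and power is about 93%.

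**8. Dropout.** 50/0.9 = 55.6, rounded up to 56. This step reproduces.

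**The case against.** The strongest case against runs as follows. The inputs do not fix a sample size, so they cannot refute 50 either. Some readings deliver 80%: 26% vs 1% under clustering; a participant-level SD of about 31 points or less; or a change score with 0.8 as the correlation over time, which fits the section's own words about a mean difference in reduction. The only other intraclass correlations in the document are examiner-reliability values of 0.75 to 0.85, so within-mouth clustering is not a certain reading. The document gives no BoP rate. Since entry requires the absence of gingival inflammation, the higher control rates in the table cannot simply be called plausible. Finally, a condensed article may leave the SD to the full protocol.

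Most of this stands, and it rules out an inference that a reader might draw: that the trial has only 50% to 75% power. That range needs control rates that the document does not give, and it leaves out both ends of the 48% to 85% found under the same reading.

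Three things remain. First, each route to 50 needs a value that the paragraph does not state. The change-score route reaches 50 only with an SD of 50 points, essentially the largest possible on a 0 to 100% scale, and gives the 200 sites no role. Second, an omitted SD alone could be left to the full protocol. Here the article prints a derivation as if it were complete, and its terms do not yield the result. Third, the site count contradicts the article's own definition of BoP recording. That the 200 came from the four microbiota sites is an inference from the number 4; the document does not say so.

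**Conclusion.** The point holds in this form: the sample size does not follow from the inputs stated for it, and it is expressed for 4 sites per mouth when the primary outcome uses about 80 to 112.

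The size of any power shortfall is conditional. With clustering at 0.8 and an absolute difference, power lies between 48% and 85% and is below 80% at most control rates. With a relative difference it is about 6% to 16% for control rates of 10% to 50%. On participant means, 80% holds only if the SD is about 31 points or less; if the change is analysed, this is the SD of the change. The documents do not show which of these applies, so they support neither a statement that the trial is underpowered nor the stated 80%.

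**What to change.** Restate the paragraph, with no added enrolment:

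- Make the participant-level percentage of bleeding sites, or its change, the unit of the calculation.
- Give the SD or control rate that was actually assumed, say whether 25% is in percentage points or relative, and say what the 0.8 refers to.
- Report what 25 completers per arm deliver: a detectable difference of 0.81 SD at 80% power, and the power for 25 points at the assumed SD.
- Remove the 200 sites, or tie them to the sites that will be analysed.

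A figure of 50% to 75% should not be published as the trial's power, because it rests on control rates that the document does not give.

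One related point should be settled in the same edit. Twenty-five completers per arm presupposes the 56 inclusions in Sample Size, while the Randomization section enrols 50. At 10% dropout, 50 would leave 45.

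The cost is the rewording of one paragraph and, possibly, a less favourable stated power.

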### Recruitment

Participants will be recruited via an existing database of healthy volunteers previously enrolled in oral health studies at the P2S laboratory (Université Lyon 1) and public announcements on social media and digital platforms of the laboratory. All participants will receive free study materials (IDBs for 3 months) and reimbursement of travel costs (2 local transportation tickets per visit).

### Randomization and Blinding

#### Randomization

Participants will be randomly assigned to one of 2 arms (arm 1: calibrated IDBs and arm 2: noncalibrated IDBs). Randomization will be performed using an interactive web response system integrated into the electronic case report form (v8.2.30 build 3, EnnovClinical Group). Allocation will be 1:1 without stratification, as the sample size is limited and the population is considered homogeneous. Participants will remain in the same arm during the study period. A total of 50 participants will be enrolled, with 25 assigned to each group.

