**Methods:**

The HIJA trial is a monocentric, randomized, controlled, single-blind, and parallel-arm study. Overall, 50 healthy, nonsmoking adults aged 18‐30 years will be randomized (1:1) to receive either calibrated or noncalibrated IDBs. Participants will perform daily interdental cleaning in addition to conventional toothbrushing for 3 months. The primary outcome will be the reduction in interdental inflammation, expressed as the change in bleeding on probing at 3 months. Secondary outcomes will assess differences in interdental microbiota composition (16S ribosomal RNA sequencing), periodontal indices (plaque index, gingival index, probing depth, and clinical attachment loss), and user acceptability measured through the Theoretical Framework of Acceptability questionnaire at 1, 2, and 3 months.

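### The protocol gives two numbers to randomize, 56 and 50; with 50, the plan's own 10% dropout leaves 45 of the 50 completers it requires and about 76% power instead of 80%

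*Protocol article*

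**What the plan says.** Three places in the protocol article give the size of the trial.

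- **Sample Size.** The calculation concludes that "a total of 50 participants (200 sites) are required". It then allows for 10% dropout: "in order to have 50 participants at the end, 56 participants (28 per group) will be included". Here 50 is the number remaining at the end and 56 is the number entering.
- **Randomization.** After describing the web-based allocation system and the 1:1 ratio, the section states: "A total of 50 participants will be enrolled, with 25 assigned to each group". Here 50 is the number entering.
- **Abstract, Methods.** "Overall, 50 healthy, nonsmoking adults aged" 18 to 30 years are to be randomized 1:1. Again 50 is the number entering.

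**The concern.** The totals differ (56 against 50) and so do the group sizes (28 against 25). The terms do not explain the difference. One might try to read the 56 as participants screened and the 50 as participants randomized, but the 56 is split by group and tied to dropout, so it is a count after allocation. Nor can the 50 in the Randomization section be a count of completers, because it is the number enrolled and assigned.

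Two things are at stake. If recruitment stops at 50, the dropout allowance is lost and the trial is expected to finish below the size its own calculation requires. Also, nobody overseeing the trial can tell from the article whether recruitment is complete at 50 or at 56. Either stopping point contradicts part of the text, and stopping at 50 could not be told apart from stopping early.

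**Working it through.** **Inputs**, all from Sample Size unless noted:

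- two-sided α = 0.05 and power 80%
- required at the end: 50, that is 25 per group at 1:1
- dropout: 10%
- to be included: 56 (28 per group)
- to be enrolled: 50 (25 per group), from Randomization; also 50 in the abstract

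**Step 1: reproduce the plan's 56.** The number to enter is the number required divided by (1 − dropout).

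- Total: 50 / 0.90 = 55.6, rounded up to 56.
- Per group: 25 / 0.90 = 27.8, rounded up to 28.

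The Sample Size section is therefore consistent with itself.

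**Step 2: expected completers under each figure.**

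| Randomized | Expected completers | Against the required 50 |
|---|---|---|
| 56 | 56 × 0.90 = 50.4 | met |
| 50 | 50 × 0.90 = 45 | 5 short |

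**Step 3: power at the smaller size.** The article gives no standard deviation (SD) and no control-group bleeding rate, so power cannot be rebuilt from its inputs. The loss relative to the plan's own claim can be. Take 80% at 50 completers as given and scale the noncentrality by the square root of the sample size.

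- Noncentrality at 50: 1.960 + 0.842 = 2.802.
- At 45: 2.802 × √(45/50) = 2.658. Power = Φ(2.658 − 1.960) = Φ(0.698) ≈ 75.7%.
- At 50.4: 2.802 × √(50.4/50) = 2.813. Power = Φ(2.813 − 1.960) = Φ(0.853) ≈ 80.3%.

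**Step 4: cross-check with a two-sample t test.** The standardized difference that gives 80% power at 25 per group is d = 0.809. This value is solved for here; it is not stated in the plan.

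- With d = 0.809 and completers split 23 and 22, power is 75.5%.
- The difference detectable with 80% power rises from 0.81 SD at 25 per group to about 0.85 SD at 23 and 22.

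The two methods agree to within 0.2 percentage points.

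**The case against.** The contradiction itself has no good defence; the case on the other side concerns how much follows from it.

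- **The shortfall is conditional.** If 56 are randomized, as Sample Size says, power is as planned. The article does not say which number the randomization list uses. This stands: what is shown is an unreconciled number, with a shortfall under one of the two readings.
- **Completers are not the analysis set.** Under Data Analysis, all randomized participants enter the intention-to-treat analysis, with multiple imputation and mixed models, and bleeding is also recorded at earlier visits. Those lost before month 3 would still contribute something. This stands in part: 75.5% is a complete-case figure, and the planned analysis may do somewhat better. Imputation does not generally restore the information lost, however, and by adding a 10% allowance the plan itself counts dropouts as lost. The per-protocol analysis, which also excludes major deviators, could be smaller still.
- **The base of 50 cannot be verified.** Without an SD or a control-group rate, the 80% at 50 has to be taken on trust, and the standardized differences above are not the plan's quantities. This is true, but the comparison is relative to the plan's own claim and needs neither missing figure.
- **The article is a condensed account.** That would excuse an omission, but here two conflicting figures are both printed as current text.

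**Conclusion.** The concern holds. Sample Size and Randomization cannot both be followed, and the abstract sides with Randomization. The 56 is the figure that follows from the plan's inputs; the 50 enrolled leaves out the dropout allowance.

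If 50 are randomized, the expected shortfall is 5 completers, and power falls from 80% to about 75.5% (t test) or 75.7% (normal approximation), a loss of a little over 4 percentage points. This rests on three assumptions: 10% are in fact lost, the plan's 80% at 50 completers is correct, and participants who drop out add no information. The loss is modest. The point still needs to be settled, because the number to randomize is a core design figure and participants cannot readily be added once recruitment has closed.

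**What to change.** Preferred: state in the abstract and in the Randomization section that 56 participants will be randomized, 28 per group, to leave 50 at the end. Check that the list in the web-based system is long enough for 56.

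If only 50 can be randomized, remove the 56 from Sample Size. State instead that about 45 completers are expected, with about 75% power if the plan's 80% at 50 is accepted.

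The preferred change costs wording in two places, a check of the randomization list, and six participants whom the Sample Size section already foresees. It should be made before recruitment closes.

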#### Blinding

The study will be conducted under single-blind conditions. Participants will not know whether they are assigned to the calibrated or noncalibrated IDB group. To maintain blinding, both types of IDBs will be identical in packaging, color, and appearance. The investigator responsible for the allocation will not be blinded. Intervention implementation will be conducted by staff independent from data collection. To ensure impartiality, during the assessment and analysis phase, statisticians, clinical research associates, and clinicians will not know the group to which the participant belongs. The identification codes will be securely held by the study monitor and will remain sealed until the conclusion of the study to maintain confidentiality and prevent bias.

### Data Collection, Management, and Analysis

#### Data Collection

A case report form, specific to the HIJA study, will be created in Lyon, France. Only data required for the protocol and scientific publication will be recorded in the case report form. Each participant will be assigned a unique identification code to label all documents, forms, and data files. Thus, data recorded by investigators for each participant will be anonymized according to the Data Protection Act. As data are collected, they must be completed by authorized persons (investigators) with their own identifiers, according to the Data Protection Act. During the entry, the data are immediately checked thanks to consistency checks. The person in charge of filing must validate and justify any value change in the electronic case report form. Entries and modifications are subject to an audit trail. The quality, exactitude, and relevance of all input data will be the responsibility of the investigator. Accordingly, each page of the patient’s must be electronically dated and signed by the investigator to confirm agreement and responsibility for the collected data.

#### Data Management

Experimental and personal data will be analyzed using a unique identification code with no directly identifiable personal data. Participants can be reidentified through a subject identification file, which will be securely maintained solely at the clinical study site. The signed informed consent documents will also be kept exclusively at the clinical study site for confidentiality and privacy purposes.

#### Data Analysis

Statistical analyses will be conducted on both the intention-to-treat and per-protocol populations. All randomized participants will be included in the intention-to-treat analysis, while the per-protocol analysis will exclude those with major protocol deviations, such as nonuse of IDBs. Missing data will be addressed using multiple imputation by chained equations with Monte Carlo Markov Chain methods, assuming data are missing at random. Descriptive statistics, including means, SDs, medians, interquartile ranges, and frequencies, will be calculated. Between-group comparisons will be performed using Student 2-tailed *t* test or the Wilcoxon test for continuous variables and the Chi-square test for categorical variables. Changes over time will be assessed using mixed linear models, with log-transformed bleeding values when appropriate. Fixed effects will include independent variables such as age, socioeconomic status, and experimental group, while subjects will be included as a random effect to account for repeated clinical bleeding measurements. Estimated coefficients for each independent variable will be tested against the null hypothesis of zero, with significance set at *P*<.05. Analyses will be performed using SPSS (IBM Corp), SUDAAN (RTI International), and R software (R Development Core Team). Exploratory analyses will also be performed to assess potential correlations between CAL and participants’ adaptation and compliance with IDB use, as evaluated through the TFA questionnaire and the compliance logbook.

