The Hygiene of Interdental Junctions in Adults (HIJA) trial is designed to address the following research question, formulated according to the Population, Intervention, Comparison, and Outcome framework: In healthy young adults aged 18‐30 years (Population, P), does the daily use of calibrated IDBs (Intervention, I) lead to a greater reduction in interdental inflammation compared with the daily use of noncalibrated IDBs (Comparator, C), measured as bleeding on probing (BoP) at 3 months (Outcome, O)?

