### Procedures and Follow-Up Schedule

Participants will attend 4 visits: baseline (T0), week 1 (T1), month 1 (T2), and month 3 (T3).

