### Outcomes

#### Primary Outcome Measures

Reduction in interdental inflammation, expressed as the proportion of sites with BoP at 3 months (T3), comparing calibrated versus noncalibrated IDBs.

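### The mixed model for repeated bleeding names only a group main effect, and the plan does not say which analysis gives the 3-month comparison

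*Protocol article*

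**What the plan says.** The Primary Outcome Measures section fixes one time point: "Reduction in interdental inflammation, expressed as the proportion of sites with BoP at 3 months (T3), comparing calibrated versus noncalibrated IDBs". The research question in the Introduction also asks about month 3. Procedures and Follow-Up Schedule sets four visits (T0 baseline, T1 week 1, T2 month 1, T3 month 3), and Table 2 has BoP recorded at all of them.

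The Data Analysis section then gives two routes to a comparison between arms:

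- A simple test: "Between-group comparisons will be performed using Student 2-tailed" *t* test or the Wilcoxon test for continuous variables. No visit is named.
- A repeated-measures model: "Changes over time will be assessed using mixed linear models, with log-transformed bleeding values when appropriate". On its terms: "Fixed effects will include independent variables such as age, socioeconomic status, and experimental group, while subjects will be included as a random effect". On its test: "Estimated coefficients for each independent variable will be tested against the null hypothesis of zero".

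Neither route is labelled the primary analysis. The terms named for the model do not include visit, group-by-visit or baseline BoP.

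**The concern.** The purpose, random effect, named fixed effects and hypothesis test of the model are all stated, and they do not fit together. Age, socioeconomic status and group are participant-level variables that do not differ between visits. A model of BoP containing only these has no coefficient that describes change over time. Its one treatment term is a group main effect, which pools the visits.

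Two things are at stake. First, if that coefficient were taken as the treatment effect, it would answer a different question from the month 3 question and could understate a difference that is present at T3. Second, the plan allows at least two treatment effects with different meanings and does not say which decides the trial. The choice could then be made after the data are seen.

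**Working it through.** **1. The plan's own figures.** Sample Size gives "Based on a 2-sided α of .05, 80% power, an intraclass correlation of 0.8, and an expected 25% difference in BoP between groups", leading to 50 participants, then 56 after 10% dropout. The dropout step reproduces: 50 / 0.9 = 55.6, rounded up to 56. The 50 can be neither reproduced nor refuted, because no SD or control BoP rate is given and the text does not say whether the 25% is absolute or relative.

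**2. Assumptions.** I take the difference as 25 percentage points at T3 with none expected at T0 (randomised arms), and 25 completers per arm (50 / 2). I then solve for the SD that gives 80% power in a two-sample comparison:

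SD = 25 / [(1.960 + 0.842) × √(2/25)] = 25 / (2.802 × 0.2828) ≈ 31.5.

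The correlation ρ between visits within a person is not given. I use 0.5, with a range of 0.3 to 0.8. The powers below depend only on the ratio 25/31.5 ≈ 0.79, so any difference and SD in that ratio give the same powers. Calculations are on the untransformed scale with complete data.

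**3. What the group coefficient estimates.** In balanced data, a random-intercept model without a group-by-visit term has a group coefficient equal to the arm difference in participants' means over the k visits entered. Its expectation is the average of the visit-specific differences. The SD of a participant mean is SD × √[(1 + (k − 1)ρ)/k]:

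- k = 4, ρ = 0.5: 31.5 × √0.625 ≈ 24.9, so the standard error of the difference is 24.9 × 0.2828 ≈ 7.05.
- k = 3, ρ = 0.5: 31.5 × √0.667 ≈ 25.8, so the standard error is about 7.29.

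Adding visit as a main effect does not change what this coefficient estimates.

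**4. Size under assumed effect profiles.** Power is for ρ = 0.5, with the range for ρ from 0.8 to 0.3 in brackets.

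| Share of the T3 effect at T0, T1, T2, T3 | T0–T3 as responses | T1–T3 as responses |
|---|---|---|
| Linear in time (weeks 0, 1, 4.3, 13): 0, 0.08, 0.33, 1 | 8.8 points, 24% (19–30%) | 11.7 points, 36% (29–44%) |
| Equal steps: 0, 1/3, 2/3, 1 | 12.5 points, 43% (33–53%) | 16.7 points, 63% (52–73%) |
| Full from week 1: 0, 1, 1, 1 | 18.8 points, 76% (63–86%) | 25.0 points, 93% (85–97%) |

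Example, equal steps with T0–T3: 25 × (0 + 1/3 + 2/3 + 1)/4 = 12.5. Then 12.5/7.05 − 1.96 ≈ −0.19, which gives 43%. In the extreme case of an effect only at T3, the four-visit coefficient would be 25/4 = 6.25 points with 14% power.

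**5. Comparators.** A T3 contrast estimates 25 points with 80% power, by construction of the SD. With adjustment for baseline BoP the SD becomes 31.5 × √(1 − 0.5²) ≈ 27.3, and power is 90% (84% at ρ = 0.3, above 99% at ρ = 0.8).

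**6. Simulation check.** In 150 simulated trials per profile at ρ = 0.5, the group-only model gave 8.6, 12.5 and 18.3 points (power 27%, 45%, 69%) for the linear, equal-step and week 1 profiles. The T3 contrast from a model with group-by-visit gave about 25 points each time (power 76% to 78%).

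**The case against.** The strongest reply has five parts.

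- **The list is open.** It is introduced by *such as*, and a model said to assess change over time presumably contains time. This stands: visit is unnamed, not shown to be absent. But a visit main effect would still leave the group coefficient as a visit average.
- **An interaction may be intended.** With group-by-visit fitted and T0 as the reference, the group-by-T3 coefficient is the between-arm difference in change at T3, and the stated test of each coefficient would cover it. This also stands, but the text names no such term and no T3 contrast.
- **The *t* test or Wilcoxon test can supply the T3 comparison.** Sample Size rests on a mean difference in reduction, which suits a two-sample test, and the mixed model could serve the secondary outcomes on evolution over T1 to T3. This is plausible, but the section names neither the visit for that test nor the primary method.
- **T0 may not be a response.** The Abstract describes the primary outcome as a change in BoP. If change is modelled, or T0 is a covariate, the dilution from T0 disappears. With T1–T3 only and a full effect from week 1, there is no dilution at all.
- **A condensed article leaves model detail to fuller documents.** That is fair for covariance structures or software. Here the article itself states a purpose, terms and a test that do not match one another.

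A reader might infer that the trial will report a diluted effect, or that its primary analysis is underpowered. The document does not support that: it does not establish that the mixed-model coefficient is the primary result. Nor would the average leave T3 out, since it runs over every visit entered, T3 included.

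**Conclusion.** The point holds in limited form. As written, the only treatment term named for the repeated-BoP model is a group main effect, which does not estimate the month 3 effect in the research question and primary outcome. The section also does not say which of its two methods gives that comparison.

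The size is conditional. The difference scale, SD, correlation and effect profiles are all assumptions. For the three profiles tabulated, with all four visits as responses, a 25-point T3 difference becomes about 9 to 19 points with 24% to 76% power, against 80% for a T3 contrast. With T1–T3 only the loss is smaller. If the effect is complete by week 1 the average has more power than the unadjusted T3 contrast (93%), though it still addresses a different quantity unless the effect is constant.

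Severity is moderate. It falls if the sponsor confirms that a T3 *t* test is the primary analysis, since the remaining gap is then the wording of a supporting model and the precision lost by not adjusting for baseline.

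**What to change.** Rewrite the model description in Data Analysis so that:

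- the response is BoP at T1, T2 and T3;
- the fixed effects are arm, visit (categorical), arm-by-visit and baseline BoP, plus age and socioeconomic status if they are to be kept;
- within-person dependence is handled by a participant random effect or another suitable covariance structure;
- the arm contrast at T3 is declared the primary test, with the T1 and T2 contrasts secondary.

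State the role of the *t* test or Wilcoxon test on BoP, for example as a supporting comparison at T3. If it was always meant to be primary, say so and name the visit. The baseline-adjusted T3 contrast is still preferable, because it uses data already collected and improves precision (90% against 80% power at ρ = 0.5 under the assumptions above).

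The cost is wording only: no new visits, measurements or participants. The change should be made and dated before unblinding.
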